#### Secondary Outcomes

The FMA-UE, CSS, and MBI were secondary outcome indicators.

The FMA-UE is often a widely used evaluation tool for evaluating upper extremity motor function during stroke rehabilitation. It can effectively, stably, and sensitively reflect the changes in patients' dysfunction with good reliability and validity (34, 35). Evaluate the flexion, coordination, range of motion, stability, and coordination of each joint of the patient's upper limb, which is composed of 33 items in four parts: hand, wrist, elbow, and shoulder, with a total score of 66. The lower the score, the more serious the upper extremity dysfunction. The minimum clinically important difference (MCID) of FMA-UE was 4.25–7.25 points (36). That is, if the difference in upper extremity motor function score before and after treatment is >MCID, it is considered that the upper extremity motor function of the patient has been improved, the treatment is effective and can surpass the random error (37).

The CSS was determined by the “Fourth National Conference on Cerebrovascular Diseases” (1995), which is mainly to evaluate the curative effect and is divided into basic cure (the score of functional defect was decreased by 91–100%, and the degree of disability was grade 0), significant effect (the score of functional defect was decreased by 46–90%, and the degree of disability was grade 1), improvement (the functional defect score was decreased by 18–45%), and ineffective (the functional defect score decreased by about 17%). The score is simple and easy to use (38).

The MBI is a standard scale that is widely used to evaluate the dysfunction of basic activities of daily living, which consists of 10 daily life activities, such as bathing, toilet, eating, and dressing, with a total score of 100. The higher the score, the better the self-care ability in daily life (39).

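### The printed category rules for two secondary outcomes cannot be applied: the CSS classes leave patients unplaced, and the FMA-UE cut-off is a range

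*Protocol article*

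**What the plan says.** All the relevant text is in the Secondary Outcomes section of the protocol article.

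**CSS.** The score is described as one "which is mainly to evaluate the curative effect and is divided into basic cure" and three further classes. The four classes are:

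- The top class, *basic cure*, needs a fall of 91–100% together with grade 0 disability.
- The second class reads "significant effect (the score of functional defect was decreased by 46–90%, and the degree of disability was grade 1", so it too needs both a band and a grade.
- The third class, *improvement*, is a fall of 18–45% and carries no grade condition.
- The lowest class reads "ineffective (the functional defect score decreased by about 17" per cent, and it also carries no grade condition.

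**FMA-UE.** The scale is "composed of 33 items in four parts: hand, wrist, elbow, and shoulder, with a total score of 66". The article states that "The minimum clinically important difference (MCID) of FMA-UE was 4.25–7.25 points". It then says that "if the difference in upper extremity motor function score before and after treatment is >MCID", the patient has improved and the treatment is effective. It does not choose a value within the range.

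No other section completes either rule. Statistical Analysis plans chi-square or Fisher tests for categorical variables and t or rank-sum tests for continuous ones. It does not say whether CSS and FMA-UE will be analysed as scores, as classes or as both.

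**The concern.** A classification should give every patient exactly one class. The CSS rule does not, for three reasons. Its lowest class is close to a single value instead of everything below 18%. Its top two classes join a percentage band and a disability grade with *and*, with no provision for a patient who meets one and not the other. Its bands are set in whole percentages, whereas a percentage change in a score is seldom whole.

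The FMA-UE rule has a different fault: for part of the scale, the answer depends on which end of the MCID range is used.

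If a rate is reported from either rule, someone must decide later where these patients go. Made after outcomes are known by arm, that decision could shape the result. Quality Control provides for an analysis at 54 patients whose results go to the lead investigator, so outcome data may be seen before the trial ends.

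**Working it through.** The plan gives no figure for either classification, so there is nothing to reproduce. The check applies the printed rules.

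**CSS, single cases.** Percentage fall = 100 × (before − after) / before. The scores are examples.

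| Before → after | Fall | Disability grade | Class as printed |
|---|---|---|---|
| 20 → 18 | 2/20 = 10% | any | none |
| 20 → 20 | 0% | any | none |
| 20 → 22 | −10% (worse) | any | none |
| 20 → 5 | 15/20 = 75% | 0 or 2 | none (grade 1 required) |
| 22 → 12 | 10/22 = 45.5% | any | none (between 45 and 46) |
| 28 → 23 | 5/28 = 17.9% | any | none, unless *about 17%* is stretched |
| 21 → 2 | 19/21 = 90.5% | any | none (between 90 and 91) |

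A fall of 91% or more with grade 1 or higher also has no class.

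**CSS, enumeration.** Assumptions: whole-point scores; baseline from 5 to a maximum of 45 (the article does not give the maximum); no worsening; grades 0, 1 and 2, with 2 standing for anything higher.

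- Before/after pairs: the sum of (b + 1) for b = 5 to 45 is 1066. With three grades this makes 3198 combinations.
- With *about 17%* taken as 16.5–17.5, 1764 of 3198 (55%) have no class. The share is also 55% for a maximum of 30 (794/1443) and of 60 (3087/5628).
- Widening *about 17%* to 15–19 still leaves 53–54%.
- The generous reading takes *ineffective* as 17% or less and rounds percentages to whole numbers. It closes the low end and the gaps between bands, but leaves 1154 of 3198 (36%). These are the 577 pairs with a fall of 46% or more, each with two of three grades failing the condition: 577 × 2 = 1154.

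These are shares of possible combinations, not of patients. They show that charitable reading of *about 17%* does not repair the scheme.

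**FMA-UE.** The maximum is 66 over 33 items, so 66/33 = 2 points per item on average; whole-point scoring is assumed.

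| Gain | > 4.25 | > 7.25 |
|---|---|---|
| 4 or less | no | no |
| 5, 6, 7 | yes | no |
| 8 or more | yes | yes |

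To illustrate the size, take the change as normal with mean m and SD s, with boundaries at 4.5 and 7.5 for whole points. The difference in responder rate is Φ((7.5 − m)/s) − Φ((4.5 − m)/s).

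- m = 6, s = 6: 1 − Φ(−0.25) = 0.599 against 1 − Φ(0.25) = 0.401, a difference of about 20 percentage points.
- Over m = 4, 6, 8, 10 and s = 4, 6, 8, the difference runs from 13 points (m = 10, s = 8) to 29 points (m = 6, s = 4).

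The means and SDs are assumptions; the article gives none.

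**Direction of any bias.** Suppose E patients are truly effective and I are not, and unplaced patients are excluded: e from the first group and i from the second. The rate becomes (E − e)/(E + I − e − i). It rises if e/(e + i) is below E/(E + I) and falls if it is above. The printed rule leaves out both non-improvers and strong improvers with a mismatched grade, so neither case can be ruled out. If unplaced patients are instead counted as not effective, the rate can only fall or stay the same. The article specifies neither treatment.

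**The case against.** The best defence is that no CSS or FMA-UE rate is named as an outcome. The abstract and Outcome Assessments list both as scores, and scores can be compared between arms without classes. On that view the categories are background on the scales. This stands in part: it limits the damage to category-based rates. It does not remove the point, because the article presents the CSS classes as the means of judging curative effect and uses the MCID to call treatment effective, and both rules fail on their own terms.

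A second defence is that if *effective* means any fall of 18% or more, a grade mismatch changes a patient's label but not the effective rate. That is correct once such a definition is written down. The article does not write it.

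Several stronger readings are tempting but unsupported:

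- A reader might infer that the gaps inflate the effective rates, because non-improvers go unplaced. Strong improvers with a mismatched grade go unplaced too, and nothing says that unplaced patients are dropped.
- A reader might infer that CSS can put one patient in two classes. The printed bands are disjoint; overlap arises only if *about 17%* is stretched to 18% or beyond.
- A reader might infer that the 65% and 85% rates in Sample Size are therefore undefined because of these rules. That section does not tie them to CSS or FMA-UE.
- A reader might take the MCID sentence as a claim that a before/after gain shows FA to be better than TA. It explains what an MCID means for a patient; Trial Design and Setting says that efficacy is compared with the control group.

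**Conclusion.** The point holds for the two category rules and no further. As printed, the CSS scheme has no class for falls clearly below 17%, no change or worsening, for falls of 46% or more with a non-matching grade, or for values between bands. The FMA-UE rule gives two answers for gains of 5, 6 and 7 points. The defect is in rules that the article states, so it is not detail left to an analysis plan.

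The consequence is moderate. Both outcomes are secondary, their raw scores remain analysable, and MAS is not affected. If an FMA-UE responder rate is reported, the open cut-off could matter: 13 to 29 percentage points within an arm under the assumed distributions. The effect on the difference between arms, and the direction of any bias in CSS rates, cannot be determined from the document. The FMA-UE result rests on whole-point scoring. The CSS conclusion does not depend on the assumed maximum score.

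**What to change.** **CSS.** Make the classes exhaustive on percentage change:

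- *ineffective*: fall below 18%, including no change and worsening
- *improvement*: 18% to below 46%
- *significant effect*: 46% to below 91%
- *basic cure*: 91% or more

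State that a patient who reaches a percentage band but not its grade condition drops to the next lower class whose conditions are all met, with *improvement* as the floor for any fall of 18% or more. For this step, treat the percentage bounds as lower limits: a 95% fall with grade 1 is then *significant effect*, and with grade 2 *improvement*. State also whether grade 1 in the second class means exactly 1 or 1 and better; otherwise a 75% fall with grade 0 would drop to *improvement*.

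**FMA-UE.** Compare the score between groups adjusted for its baseline value, in place of the plain t-test. This needs no cut-off. If a responder rate is reported, fix one cut-off before unblinding and before any interim results by arm are seen, and compare the rates between arms. One option is > 7.25 (8 points or more), the conservative end of the article's range, with > 4.25 as a sensitivity analysis. Any single value fixed in advance removes the ambiguity.

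**Cost.** Wording only, with no new data. The stricter cut-off will give lower FMA-UE responder rates.

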### Safety Evaluation and Adverse Events

During the whole treatment process, any adverse events and their treatment methods will be recorded. Adverse events associated with acupuncture treatment included severe pain, syncope, bleeding, or any other discomfort. During the intervention, researchers will pay close attention to the patient's condition. If the patient has any discomfort, the intervention will be stopped immediately and the patient's situation will be handled accordingly. Details of any medical malpractice will be reported in detail in the CRF. All adverse events will be regularly reviewed by the lead investigator, and adverse events that meet the criteria for SAEs will be reported to the local institutional review committee.

### Data Collection and Management

The data of all patients will be truthfully, accurately, and timely recorded on the CRF, such as experimental time point, result measurement, adverse events, and safety evaluation. Two independent researchers input data and keep the participants' personal information strictly confidential. The data will be safely saved by our data researchers and monitored by the ethics committee of the First Affiliated Hospital of traditional Chinese medicine of Henan University, as shown in Table 1. At the end of the test, study participants shall submit CRF in time and submit a test summary as required.

### Statistical Analysis

After all the experimental data are verified to be correct, SPSS19.0 statistical software is used for statistical analysis. Classified variables will be analyzed using Pearson's χ^2^ test or Fisher's exact test, and continuous variables will be evaluated using Student's *t*-test or an appropriate non-parametric method. The statistical results are measured by the mean ± standard deviation (SD; *x* ± s); when comparing within or between groups, tests for normality and homogeneity of variance are performed prior to data analysis for each group. If the data satisfy normal distribution and homogeneity of variance, the *t*-test will be used for comparisons between two groups, and the least significant different (LSD) or Student-Newman-Keuls (SNK) method will be used for multiple comparisons. Instead, the rank-sum test will be used for non-normality or non-uniformity of variance. Set the test level as 0.05, *p* < 0.05, and the difference was statistically significant.

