## Methods and Analysis

### Trial Design and Setting

This was a parallel design and randomized controlled trial. The subjects were be recruited from the Rehabilitation Center of the First Affiliated Hospital of Henan University of Chinese medicine. We selected 108 patients who met the predefined criteria and randomly divided them into 2 groups, with 54 patients in each group: the experimental group and the control group. All patients received 20 courses of treatment for 4 weeks, and the upper limb function was evaluated before and after treatment. The efficacy of the experimental group when compared with the control group was analyzed after data collection. An example template for the content of admission plans, interventions, and evaluations is shown in Table 1. Our protocol presentation is in accordance with the Standard Protocol Items: Recommendations for Interventional Trials 2013 (SPIRIT 2013) guidelines (30). The study flowchart is presented in Figure 1.

**Table 1 T1:** Qualification screening and informed consent was completed before the assignment.

**Timepoint**	**Enrollment**	**Allocation**	**Treatment period**			
	**−1 week**	**0 week**	**1 week**	**2 week**	**3 week**	**4 week**
Enrollment						
Eligibility screen	X					
Baseline	X					
Informed consent	X					
Medical history	X					
Merger disease	X					
Allocation		X				
Interventions						
Experiment group			X	X	X	X
Control group			X	X	X	X
Assessments						
MAS		X				X
FMA-UE		X				X
CSS		X				X
MBI		X				X
Safety evaluation		X				X
Needle sensation			X	X	X	X
Adverse events			X	X	X	X

*After allocation, each patient was treated within 4 weeks. The clinical outcome was evaluated twice: after allocation and after treatment. Adverse events were recorded on the case report form (CRF) at any time during treatment*.

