### Inclusion and Exclusion Criteria

Inclusion Criteria. The Eligible Participants Should Meet all of the Following Criteria:

(1) The patients met the diagnostic criteria of ischemic stroke and were diagnosed by computed tomography (CT) or magnetic resonance imaging (MRI).

(2) Patients with clinical symptoms of paralysis on one side of the limb and upper extremity motor dysfunction.

(3) Patients with the MAS is the grade I and above, grade III and below.

(4) Men or women with an age range between 20 and 70 years.

(5) The Brunnstrom recovery stage (BRS) of the patient's upper extremity ranged from II to IV.

(6) Patients who are stable, conscious, and have no communication problems.

(7) Patients with no previous history of upper extremity dysfunction, first onset, or legacy of stroke.

(8) The participants were voluntary and signed the relevant informed consent.

Exclusion Criteria. Criteria for Exclusion Are the Following:

(1) Patients with upper extremity motor dysfunction, combined with severe cardiovascular disease, hypertension, respiratory infection, severe renal dysfunction, severe diabetes mellitus, and a history of psychiatric, were accompanied by agnosia, apraxia, and an intellectual disability that affects communication and evaluation.

(2) Patients with unstable vital signs in the acute phase.

(3) Patients in thrombolytic therapy.

(4) Fear of acupuncture and poor physical fitness, such as easy to faint, are not suitable for acupuncture treatment of patients.

(5) Patients who have taken sedative drugs and muscle relaxants in the recent past.

(6) Patients with transient ischemic attack (TIA), reversible ischemic neurological deficits, subarachnoid hemorrhage, etc.

(7) Patients who are pregnant, lactating, or preparing for pregnancy.

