#### Primary Outcomes

The main result is the MAS, which is the most widely used clinical spasm scale (32). It is usually used to obtain the baseline evaluation of increased muscle tone, monitor the course of the disease, determine the effectiveness of drugs, and rehabilitation interventions, so as to reduce the overall increase of muscle tension, normalize the muscle tone of the selected muscle group, and guide physical therapy and other treatment decisions. It has the advantages of simplicity, time saving, and convenient operation. It is divided into 6 levels, i.e., 0, I, I +, II, III, and IV. Scoring methods, i.e., 0, 1, 2, 3, 4, and 5 points, represent 0, I, I +, II, III, and IV, respectively. The higher the MAS score, the more serious the spasticity. Compared with the lower limbs, the reliability of the upper limbs is better (33). The specific contents of MAS are shown in Table 3.

**Table 3 T3:** The modified Ashworth score (MAS)-specific scoring rules.

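### The stated between-arm comparison is chosen by a normality and variance pre-test and uses no baseline covariate, although baseline MAS is collected in every patient; the cost is power, not false positives

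*Protocol article*

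**What the plan says.** The Primary Outcomes section makes the MAS the primary outcome. On its structure it says "It is divided into 6 levels, i.e., 0, I, I +, II, III, and IV", and it turns the levels into numbers ("Scoring methods, i.e., 0, 1, 2, 3, 4, and 5 points"). The inclusion criteria limit entry: "Patients with the MAS is the grade I and above, grade III and below", which is 1 to 4 on that scoring. The note to Table 1 says "The clinical outcome was evaluated twice: after allocation and after treatment", and the table marks the MAS at week 0 and week 4, so each patient has a baseline value.

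The Statistical Analysis section then states: "when comparing within or between groups, tests for normality and homogeneity of variance are performed prior to data analysis for each group". If both conditions hold, two groups are compared by t-test. If not: "Instead, the rank-sum test will be used for non-normality or non-uniformity of variance". Results are summarised as mean and SD, categorical variables go to chi-square or Fisher's exact test, and LSD or SNK is named for multiple comparisons. No named between-group test takes a covariate. The section does not mention the MAS by name and does not say whether post-treatment values or changes are compared.

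**The concern.** Two features of the stated method fit this outcome badly.

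- **The pre-test offers no real choice.** A score with six possible values will fail a normality test at about 49 per arm almost regardless of its shape. A rule that appears to choose between two methods therefore gives one in practice, without saying so. The method is also not formally fixed before the data are seen.
- **The baseline is not used as a covariate.** Patients enter across four grades of spasticity. Where they start predicts part of where they finish, and adjusting for this removes variance from the treatment comparison at no cost in patients or visits.

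At stake is the chance of detecting a real difference between functional and traditional acupuncture, two active treatments that are both given on top of routine rehabilitation.

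**Working it through.** **1. The plan's own figure.** The Sample Size section gives 49 per group. With P = 0.65, z-values 1.645 and 1.282 and δ = 0.20: 0.65 × 0.35 × ((1.645 + 1.282)/0.20)² = 0.2275 × 214.18 = 48.7, so 49; and 49 × 1.10 = 53.9, so 54. This sizes a binary effective rate and gives no power for a MAS comparison. Only n = 49 per arm is taken from it here.

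**2. Inputs not in the document (assumptions).** SD of the MAS, its correlation ρ between baseline and week 4, and the treatment effect on it. Effects are set in SD units and ρ is varied.

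**3. Closed form, continuous approximation.** Power ≈ Φ(d/s × √(49/2) − 1.96), two-sided 5%. The residual SD is s = 1 for post scores, √(1 − ρ²) with baseline adjustment, and √(2(1 − ρ)) for change scores. Take d = 0.566, which gives the unadjusted post-score test 80% power: 0.566 × 4.950 = 2.802, and 2.802 − 1.96 = 0.842.

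| ρ | Post, unadjusted | Change | Baseline-adjusted | n per arm for 80% if adjusted, 49(1 − ρ²) |
|---|---|---|---|---|
| 0.3 | 80.0% | 65.8% | 83.6% | 45 |
| 0.5 | 80.0% | 80.0% | 89.9% | 37 |
| 0.7 | 80.0% | 95.1% | 97.5% | 25 |

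Example at ρ = 0.5: s = √0.75 = 0.866; 0.566/0.866 × 4.950 = 3.235; Φ(1.275) = 89.9%.

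**4. Simulation on six levels with the entry limit.** 49 per arm, latent effect 0.5 SD, baseline limited to scores 1-4. The adjusted model is linear in arm and baseline MAS on the 0-5 score. Two separate sets of runs:

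| ρ | Rank-sum, post | Adjusted | Gain | Rank-sum, change | Gain over change |
|---|---|---|---|---|---|
| 0.4 (set A) | 63% | 69% | 6 | 53% | 16 |
| 0.6 (set A) | 67% | 80% | 13 | 66% | 14 |
| 0.75 (set A) | 71% | 90% | 19 | 84% | 6 |
| 0.4 (set B) | 67% | 71% | 4 | | |
| 0.6 (set B) | 70% | 82% | 12 | | |
| 0.75 (set B) | 73% | 91% | 18 | | |

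In set A every simulated trial failed the pre-test and went to the rank-sum test.

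**5. Proportional-odds model.** In a smaller run with the same n, effect and entry limit (400 trials per setting, Monte Carlo error about 2.5 points), proportional-odds regression with baseline MAS reached 66% against 61% for rank-sum on post scores at ρ = 0.3, and 71% against 59% at ρ = 0.5. Rank-sum on change reached 55% and 68%; the 3-point gap at ρ = 0.5 is within simulation error.

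**6. Type I error.** Without the entry limit (3,000 trials per setting), the pre-test rule rejected a true null in 4.8-5.4% of trials. Linear ANCOVA gave 5.6%, 4.8% and 6.2% at ρ = 0.3, 0.5 and 0.7. The standard error is √(0.05 × 0.95/3000) = 0.4 points, so 6.2% is high for one setting. A separate set of 2,500 trials per setting gave 4.8-4.9% for the adjusted model and 4.3-4.6% for rank-sum. With the entry limit, error was near 5% at ρ = 0.6.

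**The case against.** The strongest defence is that the rank-sum test is valid for an ordinal score. If the rule always ends there, the method is in effect fixed and the remaining issue is efficiency. This stands: the harm is lost power, and preferring ordinal regression to ANCOVA is partly taste. It does not follow that the stated rule is adequate, since a free gain is left unused.

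Four stronger readings are tempting, and the document does not support them.

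- *Letting the data choose the test inflates false positives.* The simulations show no inflation for the pre-test rule.
- *The baseline MAS is ignored.* The text is silent on post versus change scores. With change scores the baseline is used, though less efficiently, and the gap at ρ = 0.75 shrinks to about 6 points. Nor is it certain that the t-test/rank-sum rule applies to the MAS at all. A chi-square test on the levels is possible, but it would use neither their order nor the baseline.
- *The gain is 8, 17 or 26 points* at ρ = 0.4, 0.6 and 0.75. Those figures arise if baseline is allowed to span the whole scale. The entry limit of grades I to III narrows it and reduces the gain.
- *Within-group tests or LSD/SNK would distort the conclusion.* Trial Design and Setting says the experimental group is compared with the control group. LSD and SNK have nothing to do in a two-arm trial, and neither they nor the within-group tests change a between-group result.

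A statistical analysis plan, which is not shown, might add an effect estimate or a covariate, so their absence alone is no finding. The point is that the method stated here is a pre-tested, unadjusted comparison. Doubts about the sample-size formula are a separate matter and add no weight.

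**Conclusion.** The concern holds as a matter of efficiency and should be changed. If the stated rule is applied to the 0-5 score, it amounts to an unadjusted rank-sum test. Relative to rank-sum on post scores, baseline adjustment gains about 4-6 points of power at ρ = 0.3-0.4, about 12 at 0.6 and about 19 at 0.75. Relative to rank-sum on change scores, the linear model gains about 6 points at ρ = 0.75 and more at lower ρ. These sizes rest on 49 per arm, a latent effect of 0.5 SD, baseline limited to MAS I-III, and a correlation that nobody can read from the document. The direction is firm; the size is only as good as the assumed ρ. The size also comes mainly from a linear model, with limited support from the smaller proportional-odds run.

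**What to change.** - **Primary analysis:** name one between-group analysis of week-4 MAS with arm and baseline MAS in the model, either proportional-odds regression (common odds ratio) or ANCOVA on the 0-5 score (adjusted mean difference), with a 95% CI. Keep the rank-sum test as a sensitivity analysis.
- **Scored secondary outcomes (FMA-UE, CSS, MBI):** ANCOVA with the baseline value as covariate.
- **Pre-test:** remove the normality and variance gate.
- **Tidying only:** delete LSD/SNK, and label within-group tests as descriptive.

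The cost is a change of wording: no new data, visits or patients, and the models run in standard software. Recruitment was still under way according to Trial Status, so the change should be dated and made before unblinded data are seen. The small downside is a modelling assumption, proportional odds or linearity, which the rank-sum sensitivity analysis covers.
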